### Sample Size

#### Primary Objective 1: General Population in Norway

We will identify all individuals in the National Population Register that fulfill the eligibility criteria, and among those, make a random selection to receive the Norwegian nudge (intervention 1). We power for a 1% point minimal detectable increase in uptake in the SMS arm compared to the control arm in the general population because the intervention is relatively inexpensive and might be cost-effective even with low effectiveness on coverage. To achieve this minimal detectable increase with a baseline uptake rate of 60%, a power of 0.8, and a 1-sided α of .05, we need to randomize 18,788 individuals to intervention 1. However, based on available statistics, some 20% of individuals may have received the influenza vaccine before the scheduled trial start date and will be excluded from the trial after randomization. We thus need to randomly sample at least 23,485 individuals aged 65 years or older from the entire Norwegian population (except those born in Poland or Ukraine) to be allocated to intervention 1 to be able to detect an increase of 1 percentage point (23,485×80/100=18,788). The control group will be the rest of the Norwegian population that fulfills the eligibility criteria. Currently, there are circa 1.1 million persons aged 65 years or older who reside in Norway. We use this large group as a control because it gives the study high power, the inclusion of individuals receiving standard care carries no cost, and it will provide real-world data on the entire older adult population in Norway.

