### Assignment of Interventions

Assignment of treatment arm (control, intervention 1, and intervention 2) will be randomized, automated, and concealed. The identities of the participants will not be decipherable by the data managers.

We will use an external service provider to identify the eligible study population, perform the random selection and randomization procedures, and dispatch the SMS. The provider will be selected through a tendering process. All data management by the service provider will be done in close collaboration with and under the supervision of the project group. Data management, random selection, and randomization procedures will be performed with reproducible code that includes documented and adequate software functions, preferentially in R programming (R Foundation for Statistical Computing). For the Norwegian population, individuals in intervention arm 1 will be randomly selected from the whole eligible population, while the remainder of the eligible population will serve as the control arm. Similarly, we will use complete random assignment to treatment arm for the Polish and Ukrainian populations. Examples of R functions that serve these purposes are sample_n (from the *dplyr* package) and complete_ra (from the *randomizr* package). Random selection and randomization procedures will be performed after the assessment of the exclusion criteria. The project group will inspect the randomization code before dispatching the SMS.

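### The 18,788 for Objective 1 does not follow from the stated one-sided α of .05, and its inflation to 23,485 assumes an order of exclusion and randomisation that the protocol contradicts elsewhere

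*Protocol article*

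**What the plan says.** Protocol article, Sample Size, Primary Objective 1:

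- The target difference: "We power for a 1% point minimal detectable increase in uptake in the SMS arm compared to the control arm".
- The inputs and the result: "with a baseline uptake rate of 60%, a power of 0.8", and then "a power of 0.8, and a 1-sided α of .05, we need to randomize 18,788 individuals to intervention 1".
- The control arm: "The control group will be the rest of the Norwegian population that fulfills the eligibility criteria". On its size: "Currently, there are circa 1.1 million persons aged 65 years or older who reside in Norway".
- About 20% may already be vaccinated at the start, and these people "will be excluded from the trial after randomization". For that reason 18,788 is raised to at least 23,485, a figure that the Abstract repeats.

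The Assignment of Interventions section gives the opposite order: "Random selection and randomization procedures will be performed after the assessment of the exclusion criteria". Vaccination before the dispatch date is one of the listed exclusion criteria. The opening sentence of the Objective 1 sample size section also draws the SMS arm from people who already meet the eligibility criteria.

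Statistical Methods plans 95% Wald confidence intervals.

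**The concern.** There are two separate problems in one paragraph.

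First, the significance level, power, effect and arm size are given as one consistent set, but they are not consistent. A reader cannot tell whether the trial is meant to have 80% power at a two-sided 5% level or something higher at a one-sided 5% level. A borderline result could pass a one-sided .05 test and yet have a 95% interval that includes zero. Objectives makes the remaining study objectives depend on confirming the hypotheses for primary objectives 1 to 3, so the criterion should be unambiguous before data are seen.

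Second, the step from 18,788 to 23,485 rests only on removing people after randomisation. If exclusions come first, as another section states, that step has no basis and the power statement describes the wrong number of people.

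**Working it through.** **Inputs from the protocol.** Control rate p0 = 0.60; SMS rate p1 = 0.61; difference 0.01; power 0.80 (z = 0.8416); one-sided α .05 (z = 1.645). The control arm is the rest of an eligible population drawn from about 1.1 million.

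**Assumption.** The number eligible after exclusions is not given. I use a total of 0.88 million (1.1 million × 0.8) to 1.1 million. People without a registered phone number would lower this somewhat. The result is not sensitive to it: a total of 0.6 million gives a one-sided requirement of 15,177.

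**Step 1: can 18,788 be reproduced?** Because the control group is so large, a natural formula treats its rate as fixed:

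n = [(z_α √(p0(1−p0)) + z_power √(p1(1−p1))) / 0.01]², with p0(1−p0) = 0.24 and p1(1−p1) = 0.2379.

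| α | z_α | n, fixed control rate | n, total 1.1 million | n, total 0.88 million |
|---|---|---|---|---|
| One-sided .05 (as stated) | 1.645 | 14,794.1, so 14,795 | 14,998 | 15,051 |
| Two-sided .05 | 1.960 | 18,787.7, so 18,788 | 19,119 | 19,206 |

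The last two columns use the two-sample formula with pooled variance under the null and control = total − n. The printed figure appears to the unit in the two-sided, fixed-rate cell.

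Other one-sided variants do not rescue it. Continuity correction gives about 15,100 to 15,150. The arcsine method gives about 14,975 to 15,030 when the control group is 1.1 to 0.88 million. Equal allocation gives 29,549 per arm. A one-sided requirement of 18,788 would need a control group of only about 69,000.

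**Step 2: what power does 18,788 give?** Power = Φ[(0.01 − z_α·SE0)/SE1]. SE1 = √(0.2379/n + 0.24/n_control), and SE0 is the pooled null standard error. With a total of 0.88 million, SE1 = 0.003597 and SE0 = 0.003613:

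- One-sided .05: (0.01 − 1.645 × 0.003613)/0.003597 = 1.128, so 87%. The increase detectable with 80% power is (1.645 + 0.8416) × 0.003597 = 0.0089, or about 0.89 points.
- Two-sided .05: (0.01 − 1.960 × 0.003613)/0.003597 = 0.812, so 79%.

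A total of 1.1 million gives the same rounded values.

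**Step 3: the inflation.** 18,788/0.8 = 23,485, so the arithmetic is correct. It is needed only if a fifth of the randomised arm is removed afterwards. If exclusions precede randomisation, about 23,485 are analysed, less the few who die or emigrate. With a total of 0.88 million, SE1 = 0.003226 and SE0 = 0.003240:

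- One-sided .05: (0.01 − 1.645 × 0.003240)/0.003226 = 1.448, so 93%.
- Two-sided .05: (0.01 − 1.960 × 0.003240)/0.003226 = 1.131, so 87%.

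**Step 4: the order, side by side.** The inflation sentence puts exclusion after randomisation. Assignment of Interventions puts it before. So does the first sentence of the same sample size section, and so does the calculation for Objectives 2 to 4, which subtracts already vaccinated immigrants before counting those to be randomised. Statistical Methods names only death and emigration during follow-up as reasons to leave a randomised person out.

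**The case against.** The strongest reply is that nothing is lost. At the stated one-sided .05 the plan has more power than it claims, and 23,485 is given as a minimum. Even at two-sided .05 with 18,788 analysed, power falls short of 80% by about one point. This stands, and it limits the severity.

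Four stronger readings are tempting, and the document does not support them:

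- **That the trial was certainly sized at two-sided .05.** The match is exact only with the control rate treated as fixed. There is another route: a one-sided requirement near 15,030 divided by 0.8 also gives 18,788, which would mean that the 20% allowance was applied twice. The text does not settle which. One-sided .05 is also stated for Objectives 2 to 4, and the hypotheses are directional, so keeping the one-sided level is a legitimate choice.
- **That the immigrant groups were sized at a different error rate.** The protocol says only that their detectable increases are adjusted for three comparisons. One-sided .05/3 gives 1.94 (Ukraine) and 4.16 (Poland) points, and one-sided .025 unadjusted gives 1.82 and 3.92. Both pairs round to the printed 2 and 4.
- **That the order of exclusion changes who is compared.** Prior vaccination is a registry fact fixed before dispatch. With one cut-off date for all arms, excluding before or after randomisation leaves the same eligible population and a fair comparison. Only the arm size changes.
- **That the planned 95% intervals fix the test as two-sided.** They fit a two-sided level but do not by themselves decide the sidedness used for sizing.

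**Conclusion.** The point holds on both counts, with moderate severity. The stated α, power, effect and arm size for Objective 1 cannot all be true: the stated inputs need about 14,800 to 15,050, and 18,788 is about 25% to 27% more (18,788/15,050 = 1.25; 18,788/14,795 = 1.27). The inflation to 23,485 contradicts the stated order of exclusion and randomisation.

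Both discrepancies are conservative. Power for a 1-point increase runs from about 79% (two-sided .05, 18,788 analysed) to about 93% (one-sided .05, about 23,485 analysed), so Objective 1 is not materially underpowered. These figures rest on the protocol's 60% baseline and on the assumed total of 0.88 to 1.1 million.

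**What to change.** 1. State one α and sidedness for Objective 1, with the power that goes with it. Either keep one-sided .05 and give about 87% power at 18,788, or state two-sided .05, consistent with the planned 95% intervals, and give about 79% at 18,788 or about 87% at 23,485.
2. Make the Objective 1 sample size section and Assignment of Interventions agree on whether already vaccinated people are excluded before or after randomisation, with one vaccination cut-off date for all arms.
3. Restate the power for the number that will actually be analysed under that order.

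The cost is about two sentences. The number of messages sent need not change.

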#### Primary Objectives 2-4: Immigrants Born in Poland or Ukraine

To maximize power among individuals born in Poland or Ukraine, we will include all eligible individuals and randomly assign them 1:1:1 to each of the 3 study arms. The number we will be able to include in the trial will most likely be higher in 2025 than in 2023 (Table 1) due to the age structure in these immigrant populations and due to new migration. Based on current national demographic statistics, we anticipate there will be some 6000 individuals aged 65 years or older from each immigrant group at the start of the trial. However, some 10% may be excluded due to not having a registered phone number, and a further 1% and 6% (Table 1) may be excluded due to influenza vaccination before the scheduled SMS dispatch date among the Ukrainian and Polish immigrant populations, respectively. Thus, we expect to be able to randomize 5346 Ukrainian immigrants, giving 1782 individuals in each study arm. With a baseline uptake rate of 3% (Table 1), a power of 0.8, and a 1-sided α of .05, this gives a minimal detectable coverage increase of 2 percentage points, adjusted for 3 pairwise comparisons. Similarly, we expect to be able to randomize 5076 Polish immigrants, giving 1692 individuals in each study arm. With a baseline uptake rate of 19% (Table 1), a power of 0.8, and a 1-sided α of .05, this gives a minimal detectable coverage increase of 4% points, adjusted for 3 pairwise comparisons.

In conclusion, the minimal detectable coverage increases of this trial fall within the range of effect sizes reported for other modes of nudging investigated in neighboring countries that share a similar influenza vaccination policy. Specifically, a recent study from Denmark reported that nudging by electronic letters increased coverage by approximately 1% points [26], while a recent study from Finland reported that nudging by ordinary mail on average increased coverage by approximately 6% points [25].

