### Objectives

The primary objectives of the InfluSMS trial are to establish whether (1) influenza vaccination nudging by SMS in the Norwegian language increases influenza vaccine coverage compared to standard care, among the Norwegian population aged 65 years and older; (2) influenza vaccination nudging by SMS in Polish or Ukrainian language increases influenza vaccine coverage compared to standard care, among older adults of Polish or Ukrainian background, respectively; (3) influenza vaccination nudging by SMS in Norwegian language increases influenza vaccine coverage compared to standard care, among older adults of Polish or Ukrainian background, respectively; and (4) influenza vaccination nudging by SMS in Polish or Ukrainian language increases influenza vaccine coverage more than nudging by SMS in Norwegian language among older adults of Polish or Ukrainian background, respectively.

For primary objectives 1-3, we hypothesize that SMS nudging will increase coverage. If this hypothesis is not confirmed, the interventions investigated here are futile from a public health perspective, and the remaining study objectives will not be investigated. For primary objective 4, we hypothesize that an SMS in the official language of the native country of each immigrant population will be more effective in increasing coverage than an SMS in Norwegian.

The secondary objectives are to establish whether (1) the effect of SMS nudging in the Norwegian language differs by country background; (2) the effect of SMS nudging in the official language of their native country differs between older adults of Polish or Ukrainian background; (3) SMS nudging for influenza vaccination is cost-effective compared to standard care; (4) SMS nudging for influenza vaccination influences coverage of COVID-19 vaccination; and (5) the time to vaccination differs by the comparisons described in the primary objectives.

Secondary objectives 1-4 are exploratory and have no hypotheses. For secondary objective 5, we hypothesize that SMS nudging will shorten the time elapsed to vaccination.

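### The three-way adjustment planned in each immigrant population uses neither the stated order of objective 4 nor the logical link between the comparisons; if tests are run that way, they are valid but lose power for objectives 3 and 4

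*Protocol article*

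**What the plan says.** In each immigrant population there are three one-sided comparisons: native-language SMS versus control (objective 2), Norwegian SMS versus control (objective 3) and native-language versus Norwegian SMS (objective 4).

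- **Sample Size, Primary Objectives 2-4.** The Ukrainian inputs are "With a baseline uptake rate of 3% (Table 1), a power of 0.8, and a 1-sided α of .05" with 1782 per arm, and the conclusion is that "this gives a minimal detectable coverage increase of 2 percentage points, adjusted for 3 pairwise comparisons". The Polish inputs are "With a baseline uptake rate of 19% (Table 1), a power of 0.8, and a 1-sided α of .05" with 1692 per arm, and "this gives a minimal detectable coverage increase of 4% points, adjusted for 3 pairwise comparisons". The method of adjustment is not named.
- **Objectives.** If the hypothesis for objectives 1-3 is not confirmed, "the remaining study objectives will not be investigated". Objective 4 therefore comes after the control comparisons. Its direction is fixed: "we hypothesize that an SMS in the official language of the native country of each immigrant population will be more effective". Whether confirmation needs both control comparisons or only one is not said.
- **Statistical Methods.** Differences are reported with 95% Wald intervals. No rule for testing the three comparisons appears.
- **Discussion.** The detectable effects of about 4 and 2 points are listed as a limitation, because smaller effects could still matter for an inexpensive intervention.

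**The concern.** An equal three-way split treats the comparisons as three unrelated tests performed side by side. The plan describes something else: objective 4 is looked at only after the control comparisons, and the three null hypotheses constrain one another. A procedure that uses this structure can hold the same one-sided family-wise .05 and reject more often.

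The stake is power where the trial has no other way to gain it. All eligible Polish- and Ukrainian-born residents are already to be randomized, so the sample cannot grow, and the protocol itself calls the detectable effects a limitation. The testing rule is the lever left.

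**Working it through.** **Inputs (Sample Size section).** One-sided α = .05 and power .80. Ukrainian: 6000 × .90 × .99 = 5346, or 1782 per arm, baseline 3%. Polish: 6000 × .90 × .94 = 5076, or 1692 per arm, baseline 19%. Coverages in the SMS arms are not given and are assumed below.

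**Step 1: the plan's own figures.** The detectable increase d solves d = (z(1−a) + z(.80)) × √{[p(1−p) + (p+d)(1−p−d)]/n}, with z(.80) = .842.

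| One-sided level a | z(1−a) + .842 | Ukrainian | Polish |
|---|---|---|---|
| .05/3 = .0167 | 2.128 + .842 = 2.970 | 1.94 | 4.16 |
| .025 | 1.960 + .842 = 2.802 | 1.82 | 3.92 |
| .05 | 1.645 + .842 = 2.487 | 1.59 | 3.46 |

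Polish check at .0167: √[(.1539 + .2316 × .7684)/1692] = .0140, and × 2.970 = .0416. So .05/3 gives the stated 2 and 4 points after rounding. The match is to whole points only: power at exactly 2 and 4 points is 82.1% and 76.7%. The .025 row, which equals an unadjusted two-sided .05, also rounds to 2 and 4, but it does not fit the stated one-sided, adjusted design. The unadjusted one-sided row would give 3 for the Polish population.

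**Step 2: the logical link.** Let H2, H3 and H4 be the nulls of objectives 2, 3 and 4. If Norwegian is no better than control (H3) and native is no better than Norwegian (H4), then native is no better than control (H2). Hence when H2 is false, at most one of H3 and H4 is true.

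**Step 3: a rule that uses the link and the order.** Test H2 and H3 each at .025. If H2 is rejected, test H3 and H4 each at .05. If only H3 is rejected, test H2 at .05 and, if that is rejected, H4 at .05. Family-wise error by configuration of true nulls:

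- All three, or H2 and H3: an error needs a first-step rejection, at most .025 + .025 = .05.
- H2 and H4: H4 is reached only after H2 is wrongly rejected, at most .05.
- H3 alone or H4 alone: one true null tested at no more than .05.
- H3 and H4 without H2, or H2 alone: logically impossible.

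**Step 4: no rejection is lost against the equal split with the same order.** Read confirmation as either control comparison. The only doubtful case is Norwegian beating control and native beating Norwegian, both at .0167, with native versus control not rejected at .0167. But the native-minus-control difference is the sum of those two differences, so it clears .05 and H4 is reached. Simulation (400,000 runs, Wald z) found no lost rejection and a family-wise rate of about .05 or below.

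**Step 5: size of the gain.** Power, equal split → step-down, either-reading:

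| Control/Norwegian/native | Norwegian vs control | Native vs Norwegian |
|---|---|---|
| Polish 19/21/25% | .25 → .42 | .74 → .87 |
| Polish 19/23/27% | .77 → .89 | .71 → .85 |
| Ukrainian 3/4/6% | .31 → .49 | .73 → .86 |
| Ukrainian 3/5/7% | .83 → .92 | .65 → .81 |

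If confirmation means both control comparisons, native versus Norwegian goes from .13 to .33 (Polish 19/21/25%), from .50 to .74 (Polish 19/23/27%) and from .50 to .73 (Ukrainian 3/5/7%). Under that reading the gate itself takes the equal-split power from .71 to .50 (Polish 19/23/27%) and from .65 to .50 (Ukrainian 3/5/7%).

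**The case against.** The strongest reply is that the criticised procedure is not in the document. The adjustment appears only as a planning assumption, no method is named, and the analysis section gives 95% intervals without a .05/3 rule. Planning on an equal split and then testing with a step-down is ordinary practice, and the choice could sit in an analysis plan that is not shown. This stands in part: a reader might infer that the trial will test at .05/3 and has already lost power, and the article does not establish that. It does not remove the point. Running all three tests unadjusted at one-sided .05 would have a family-wise rate of about .126 when all arms are equal, which is not the adjusted design that the sample-size text describes. Naming the step-down either recovers power or delivers the adjustment claimed.

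Two further inferences are tempting and go too far.

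- *The loss falls mainly on the language comparison.* With the either-reading, objective 3 gains more than objective 4 in the Polish 19/21/25% case (+.17 against +.13), and the balance shifts with the assumed coverages.
- *The equal split buys nothing in error control.* With H3 or H4 the only true null, it holds the error near .017, while the step-down lets it rise to at most .05. The equal split also has simpler matching intervals, which matters when absolute differences with intervals are the main focus.

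**Conclusion.** The point holds as an efficiency improvement. An equal three-way adjustment, if used for testing, is valid, but it is dominated by a step-down that follows the plan's own order and the link between the nulls. The gain is roughly 9 to 18 percentage points of power for objectives 3 and 4 in the scenarios tabulated.

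What it rests on:

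- The equal split is inferred from the stated one-sided α and the rounded 2 and 4 points.
- The SMS-arm coverages are assumptions. The error bound does not depend on them.
- The no-loss comparison is with the equal split combined with the order in the Objectives section, confirmation read as either control comparison. Against an equal split with no order, objective 4 could lose slightly in some cases, because it could then be claimed with no control comparison confirmed; the Objectives section excludes that.
- A full .05 test has a detectable increase 2.487/2.970 = .837 of that at .05/3, worth about 1/.837² = 1.43 times the people per arm. That applies only once earlier rejections have opened that level, not to every comparison.

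A reader should not conclude that the plan fails to control error in the sample-size section, or that the planned 2 and 4 points are wrong.

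**What to change.** 1. In Statistical Methods, state one closed step-down per immigrant population at family-wise one-sided .05. Test native versus control and Norwegian versus control each at .025. If native versus control is rejected, test Norwegian versus control and native versus Norwegian each at .05. If only Norwegian versus control is rejected, test native versus control at .05 and, if rejected, native versus Norwegian at .05.
2. In Objectives, say whether confirmation means both control comparisons or either one. If both, native versus Norwegian is tested only after both rejections.
3. In Sample Size, name the adjustment and restate the detectable increases against control: about 3.9 points (Polish) and 1.8 (Ukrainian) at the first step, and 3.5 and 1.6 once a test is made at .05. For native versus Norwegian, show the assumed Norwegian-arm coverage, since that figure depends on it.

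The cost is wording and a few lines of R, with no added participants or data. The downsides are more complex matching confidence intervals and an error of up to .05, instead of .017, when a single null is true. The rule should be fixed before outcome data are seen.
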